## Abstract

**Background:**

Polycystic ovary syndrome (PCOS) is a reproductive-metabolic condition. Insulin resistance is a hallmark of PCOS and is related to increased hyperandrogenism that drives inherent metabolic, reproductive and psychological features of the syndrome. Insulin resistance in women with PCOS is managed by weight loss, lifestyle interventions (i.e. exercise, diet) and insulin-sensitising medications. This manuscript describes the protocol of our study evaluating the effectiveness of high intensity intermittent training (HIIT) or moderate intensity exercise on cardiometabolic, reproductive and mental health in overweight women with PCOS.

**Methods/design:**

We will employ a three arm, parallel-group, randomised controlled trial recruiting 60 women diagnosed with PCOS, aged between 18 and 45 years and with a body mass index (BMI) greater than 25 kg/m^2^. Following screening and baseline testing, women will be randomised by simple randomisation procedure using computer generated sequence allocation to undergo one of two 12-week supervised interventions: either HIIT or moderate intensity exercise (standard supervised exercise), or to standard care [Con] (unsupervised lifestyle advice) at a 1:1:1 allocation ratio. The primary outcome for this trial is to measure the improvements in metabolic health; specifically changes in insulin sensitivity in response to different exercise intensities. Baseline and post-intervention testing include anthropometric measurements, cardiorespiratory fitness testing, reproductive hormone profiles (anti-müllerian hormone and steroid profiles), metabolic health, health-related quality of life and mental health questionnaires and objective and subjective lifestyle monitoring. Reporting of the study will follow the CONSORT statement.

**Discussion:**

This trial aims to demonstrate the comparative efficacy and maintenance of different exercise intensities to advance the understanding of PCOS management and provide insight into the optimal exercise intensity for improved cardiometabolic outcomes. Secondary outcomes will include the impact of different exercise protocols on reproductive hormone profiles, mental health and health-related quality of life.

**Trial registration:**

Australian New Zealand Clinical Trials Registry, ACTRN12615000242527. Registered on 17 March 2015.

**Electronic supplementary material:**

The online version of this article (10.1186/s13063-019-3313-8) contains supplementary material, which is available to authorized users.

## Background

Polycystic ovary syndrome (PCOS) is a major public health concern affecting 6–10% of reproductive-aged women worldwide [1]. Insulin resistance is strongly implicated in the aetiology of PCOS and is associated with the reproductive and metabolic consequences of the syndrome [2–7]. Insulin resistance in PCOS is inherent and has been demonstrated to be independent of body mass index (BMI), yet can be exacerbated by obesity [2, 8], although the mechanisms remain unclear. Lifestyle interventions (diet, exercise and/or behavioural) and weight management are the first line therapy [9] for women with PCOS as they improve the clinical symptoms by increasing insulin sensitivity in these women [4, 10].

Moderate intensity aerobic exercise improves metabolic and reproductive features, body composition and psychological well-being in overweight women with PCOS [4, 11, 12]. However, even after exercise interventions a higher level of insulin resistance prevails in women with PCOS compared to women without PCOS, indicating further research is warranted [4]. High intensity interval training (HIIT) is a popular fitness program that encompasses short bouts of high intensity exercise interspersed with active recovery [13]. HIIT has been shown to be acceptable and safe and may assist in addressing barriers reported in women of reproductive age, including time limitations and competing commitments and PCOS-specific barriers such as low confidence and physical limitations [14, 15]. HIIT is enjoyable [4, 16–18] and has been found to have a superior effect on insulin resistance, cardiovascular risk factors and all-cause mortality amongst other predominantly male and older clinical populations [19–22]. Despite this, there is limited comprehensive research on the efficacy of different exercise intensities and optimal exercise intensity for improved cardiometabolic outcomes, reproductive hormone profiles, mental health and health-related quality of life following exercise in PCOS.

Compared to recommended lower-intensity regimes, more positive metabolic health outcomes are now being reported for HIIT, including improved glycaemic control and cardio-respiratory fitness in clinical populations and amongst women with PCOS [17, 18, 22–24]. Only one randomised controlled trial (RCT) has been conducted in women with PCOS to assess the benefits of HIIT, in which they compared a resistance-training program and a control group [18]. After 10 weeks, they found improvements in insulin sensitivity and high-density lipoprotein cholesterol and a decrease in fat percentage [18]. A cross-sectional study conducted by Greenwood et al. [23] was the first to examine the effect of exercise of varying intensities amongst women with PCOS. The results of their study supported superior health benefits of vigorous exercise, including a lower BMI and Homeostatic Model Assessment of Insulin Resistance (HOMA-IR) and higher levels of high-density lipoprotein and sex hormone binding globulin compared with moderate exercise in women with PCOS, independent of age, BMI and total exercise volume [23]. Specifically, it was found that 60 min of vigorous activity per week was associated with a 22% reduction in the odds ratio of metabolic syndrome (1.11; 95% confidence interval 1.04, 1.18) [23]. Although these studies provide positive results in favour of high intensity exercise, more objective data and further investigation are required to find the optimal intensity in promoting the greatest health benefits for women with PCOS. Therefore, the aim of this protocol paper is to detail an exercise intervention that explores the clinical effectiveness and efficacy of HIIT compared to moderate intensity exercise or standard care (unsupervised lifestyle intervention) on metabolic (body composition and insulin sensitivity), reproductive (anti-müllerian hormone [AMH] and steroid profiles) and mental health (depression and health-related quality of life) in women with PCOS.

## Methods/design

### Hypothesis

Based on previous literature, we hypothesise that HIIT will result in greater health outcomes such as greater insulin sensitivity, increased lean muscle mass, decreased androgens, increased sex hormone binding globulin and improved mental health, and health-related quality of life compared to moderate intensity exercise or standard care.

### Design

We will employ a three-arm, parallel-group, RCT (Fig. 1) and recruit 60 women diagnosed with PCOS from the community and health clinics that are located in Melbourne, Australia, via advertisement flyers in local media, information boards in clinics and PCOS websites. They will be randomised to undergo one of three 12-week supervised interventions: either HIIT, standard supervised exercise (SSE), or standard care [Con] (unsupervised lifestyle advice) with a 6-month and 12-month post-intervention follow-up for selected endpoints.

**Fig. 1 Fig1:**
[figure not shown]
SPIRIT flow diagram of randomised control trial. *GXT* graded exercise test, *ECG* electrocardiogram, *Insulin clamp* hyperinsulinemic-euglycemic clamp, *DXA* dual energy x-ray absorptiometry, *HIIT* high intensity intermittent training, *SSE* supervised standard exercise, *Con* control

### Inclusion criteria

Women aged 18–45 years with a BMI greater than 25 kg.m^2^ and diagnosed with PCOS using the Rotterdam criteria [25] will be recruited for this study. Their medical practitioner will have previously diagnosed PCOS and the research endocrinologist will confirm this prior to participation in the study. Diagnosis of PCOS by the Rotterdam criteria requires confirmation of two of the following: (i) oligo- or anovulation; (ii) clinical (hirsutism and acne) and/or biochemical hyperandrogenism; (iii) polycystic ovaries on ultrasound and exclusion of other causes of hyperandrogenism [25]. Features of PCOS will be recorded to allow phenotyping as recommended by the National Institutes of Health [26].

### Exclusion criteria

Exclusion criteria will be other causes of menstrual disturbance and hyperandrogenism, known cardiovascular (cardiac arrhythmias), uncontrolled hypertension (resting systolic blood pressure > 160 mmHg and/or diastolic blood pressure > 105 mmHg), bleeding disorders, skin or anaesthetic allergies, musculoskeletal injuries that may be aggravated by the exercise protocol, pregnancy, type 1 or 2 diabetes or taking anti-hypertensive, insulin sensitising, anti-obesity or hormonal contraceptive medications.

### Screening

Prospective participants will be screened to check eligibility and to assess potential risks of adverse events during exercise. If identified as having multiple risk factors (family history [first-degree] of cardiometabolic risk factors, chronic conditions [that do not exclude from participation] but could interfere with testing or exercise, or have a BMI > 40 kg.m^2^), exercise clearance will be required by their general practitioner. A member of the research team will obtain written informed consent from all participants prior to participation in the study.

### Data monitoring

Details of procedures for data management have been reviewed and approved by the Victoria University Human Research Ethics Committee (reference HRE15–298). All electronic data will be stored on password-protected computers. Hard copies of any data will be kept in locked filing cabinets in a secure office. All questionnaire data will be de-identified.

#### Harms

All adverse events associated with the study will be recorded and be reported to the Victoria University Human Research Ethics Committee.

#### Auditing

No formal auditing process is proposed for the current trial. The principal investigator, [name], has extensive experience as a lead research investigator in numerous human clinical trials and is responsible for the integrity of the current trial and [3, 12, 27].

### Ethics

The study has been approved by the Victoria University Human Research Ethics Committee (reference HRE15–298) and is registered with the Australian New Zealand Clinical Trials Registry (ACTRN12615000242527). Any modifications or changes to the protocol will be provided in writing to the Victoria University Human Research Ethics Committee for approval. The study protocol was designed in accordance with the SPIRIT checklist (Additional file 1). Reporting of the study will follow the CONSORT statement [28].

### Baseline assessment

Baseline assessment will involve three sessions. Two sessions will be required to complete a symptom-limited graded exercise protocol (the first session being a familiarisation of the test). In the 7 days preceding session three, participants will wear an Actigraph™ accelerometer to establish levels of habitual physical activity. The third baseline session will involve a muscle biopsy from the vastus lateralis, an adipose tissue biopsy from the subcutaneous abdominal tissue and a hyperinsulinemic-euglycemic clamp. Participants will also undergo a dual x-ray absorptiometry scan (DXA; GE Lunar iDXA) and be asked to complete validated questionnaires to assess physical activity (International Physical Activity Questionnaire [IPAQ]) [29], quality of life (SF-36 & PCOSQ) [30, 31], depression, anxiety and stress (Depression Anxiety Stress Scale [DASS-21]) [32] and a 3-day food diary.

### Randomisation and blinding

Following baseline testing, participants will be randomised to one of three 12-week interventions; HIIT, SSE or Con (details of the three treatment arms in Table 1). An independent biostatistician will randomise subjects by a simple randomisation procedure using computerised sequence generation with an allocation ratio of 1:1:1. Two tables based on BMI (< 35 kg.m^2^ or > 35 kg.m^2^) will be created. As exercise interventions cannot be blinded from participants and staff (accredited exercise physiologists) implementing the intervention, only staff undertaking sample analysis and endpoint data processing will be blinded to group allocation.

**Table 1 Tab1:** Details of the three treatment arms

Intervention	Details
Con	Standard care consisting of basic exercise advice (150 min/week) with no supervised or structured exercise. We do not anticipate the control group will engage in a significant amount of exercise compared to their baseline physical activity levels without the addition of a structured exercise program [11]
SSE group	Minimum physical activity recommendations (150 min per week) [40], in three supervised 50-min sessions/week of continuous moderate intensity exercise sessions of cycling at 50–60% HRR (~ 3.5 METs)
HIIT group	Minimum vigorous physical activity recommendations (~ 75 min per week) [40], in three supervised sessions/week of HIIT exercise (cycling/running). Based on existing literature, pilot data [43] and patient consultation, we will use a practical weekly training program encompassing two successful HIIT protocols [16, 17, 55]: two sessions/week of short constant load cycling of 12 × 1 min at > 85% HRR (> 9 METs; [1 min HIIT]) with 1 min active recovery; one session/week of cycling 6–8 × 4 min at > 85% HRR (> 9 METS; [4 min HIIT]) with 2 min active recovery

*Con* control- standard care, *SSE* supervised standard exercise, *HIIT* high-intensity intermittent training, *min* minutes, *MET* metabolic equivalent task, *HRR* heart rate reserve

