### Statistical methods and determination of sample size

Primary analyses will be undertaken on an intention-to-treat basis, including all participants as randomised, regardless of treatment actually received. The HIIT group will be compared with the SSE and Con groups using a planned contrast of change from baseline to the week 12 endpoint on the basis of insulin sensitivity scores using a mixed-model repeated measures analysis. Stratification variables will be evaluated and retained in analyses where they are measured as significant or quasi-significant. Transformation of scores, including categorisation, may be undertaken to meet distributional assumptions and accommodate outliers. Comparisons of changes in insulin sensitivity scores from baseline to other time points will be undertaken as secondary analyses. Data will be analysed by SPSS and significance will be accepted when *p* < 0.05. Where required *p* values from the statistical analysis will be adjusted for multiple comparisons using the false discovery rate [49] and statistical significance will be accepted when false discovery rate q < 0.1.

Using the primary outcome of change in insulin sensitivity (as measured by the glucose infusion rate) of 27 mg/min/m^2^ (effect size (Cohens d) = 0.25) in response to training [4], we require a total of 42 participants or *n* = 14 per group to achieve a power of 85% (α = 0.05). With an approximate attrition rate of 30% based on previous research, we will recruit 60 participants [4, 12].

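### Simple randomisation within two BMI tables balances neither BMI nor arm size, so the stratification the protocol describes cannot work as written

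*Protocol article*

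**What the plan says.** Randomisation and blinding in the protocol article gives the method: "An independent biostatistician will randomise subjects by a simple randomisation procedure using computerised sequence generation with an allocation ratio of 1:1:1". The next sentence reads: "Two tables based on BMI (< 35 kg.m^2^ or > 35 kg.m^2^) will be created". The abstract describes the method in the same terms: "women will be randomised by simple randomisation procedure using computer generated sequence allocation". Neither place mentions blocks, minimisation or any other restriction on the sequence.

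Statistical methods and determination of sample size refers to stratification variables and keeps them in the analysis only if they prove significant or nearly so. The same section says "we require a total of 42 participants", that is 14 per group, and then: "With an approximate attrition rate of 30% based on previous research, we will recruit 60 participants". That presumes about 20 women per arm.

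Eligibility, under Inclusion criteria, is: "Women aged 18–45 years with a BMI greater than 25 kg.m^2^ and diagnosed with PCOS using the Rotterdam criteria". No upper BMI limit is stated there, so a woman at exactly 35 is eligible but belongs to neither table.

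**The concern.** Stratifying the allocation balances a factor only if the list inside each stratum is restricted, for example by permuted blocks. The article names an unrestricted method twice and describes strata once. Taken together, these statements describe a stratified design with none of the balance that stratification is meant to give.

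What is at stake is chance imbalance in a small three-arm trial, both in arm size and in BMI. The Background says obesity can worsen insulin resistance in PCOS, and clamp-measured insulin sensitivity is the primary outcome, so BMI is a reasonable factor to balance. The analysis does not reliably make up for a chance imbalance, because the BMI stratum stays in the model only if it passes a significance screen.

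**Working it through.** **Inputs.** From the article: 60 women, three arms at 1:1:1, simple randomisation, BMI tables split at 35, 42 evaluable women (14 per group), 30% attrition. Not in the article: the share of women above BMI 35, taken here as 30%, 40% and 50%.

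**The plan's own figure.** 42 / (1 − 0.30) = 60, and 60 / 3 = 20 per arm. The recruitment target reproduces.

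**Why the tables add nothing to balance.** Under simple randomisation each woman is assigned to an arm with probability 1/3, independently of all others. Any particular sequence of 60 assignments has probability (1/3)^60 from one list. From two lists of sizes h and 60 − h it has probability (1/3)^h × (1/3)^(60−h) = (1/3)^60. The two schemes have the same distribution for any BMI share.

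**Arm sizes**, Multinomial(60; 1/3, 1/3, 1/3). The SD of one arm is √(60 × 1/3 × 2/3) = 3.65, and its 95% range is 13 to 27.

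| Event | Probability |
|---|---|
| Exactly 20/20/20 | 1.4% |
| Smallest arm 15 or fewer | 32% |
| Smallest arm below 14 before any dropout | 10% |
| Largest minus smallest arm 10 or more | 29% |

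**BMI balance** (simulated), largest between-arm gap in the share above BMI 35.

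| Assumed share above 35 | Mean gap, two tables | Mean gap, one list | Gap of 20 points or more, two tables | Gap of 20 points or more, one list |
|---|---|---|---|---|
| 30% | 17.9 points | 17.9 points | 38% | 38% |
| 40% | 19.1 points | 19.1 points | 43% | 43% |
| 50% | 19.4 points | 19.4 points | 43% | 43% |

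At 50% the figure is 43% or 44%, depending on whether gaps of exactly 20 points are lost to rounding. Hence the range 38-44%.

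**What blocking would give.** With permuted blocks inside each table and an incomplete last block allowed, arm sizes differ by at most 2 (blocks of 3) or 4 (blocks of 6). In the splits that were run, the BMI-share gap was at most about 5 or 10 points respectively, and never reached 20.

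**Cost in precision.** The variance of a two-arm contrast relative to 20/20/20 is (1/n1 + 1/n2) / (1/20 + 1/20). Enumerated over the multinomial, its mean is 1.037 and its median 1.025. It is 1.15 or more in about 14% of trials and 1.23 or more in about 5%. A contrast with 85% power at 20/20/20 would average 83.7%.

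**With 30% random attrition.**

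| | Simple randomisation | Starting from 20/20/20 |
|---|---|---|
| Some arm below 14 completers | 92% | 77% |
| Some arm below 10 completers | 23% | 5% |
| Average power, if 14 v 14 gives 85% | 82.9% | 84.2% |

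The cut-off of 10 completers is illustrative and does not come from the article.

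**The case against.** The strongest reply is that the imbalances sound worse than they are. Simple randomisation is valid, and its chance imbalance is already allowed for in the test's error rate. The average loss is about 4% in variance, or a little over one point of power. Even an arm of 15 against an arm of 25 raises the variance by only (1/15 + 1/25) / 0.1 − 1 = 6.7%. The primary analysis uses change from baseline in a repeated-measures model, which deals with part of any baseline difference. All of this stands, and it rules out several stronger readings that a reader might infer:

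- **That BMI imbalance biases the comparison or could pass for a treatment effect.** Allocation is unbiased, and nothing in the article turns a BMI gap into a bias in insulin sensitivity.
- **That the planned 14 per group is lost because of simple randomisation.** Perfectly equal arms would still leave some arm short of 14 completers in 77% of trials.
- **That BMI is the main prognostic factor.** The article does not say so. The Background calls insulin resistance in PCOS independent of BMI, though worsened by obesity.
- **That the tables serve no purpose at all.** They define a variable that the analysis may use. What they do not do is balance the arms.

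A second reply is that the word simple may be loose: separate tables, a 1:1:1 ratio and equal planned group sizes suggest balanced lists, and a condensed article may omit block details. This is plausible but does not rescue the text. The omission of a block size would be no fault; naming an unrestricted method twice alongside strata is a contradiction in what is stated.

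A third reply is that blocking makes allocation more predictable in a trial where participants and exercise staff know the arms. In a block of 3 the last assignment is fully determined for anyone keeping track. This is a real trade-off, and it bears on how the blocks are chosen.

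**Conclusion.** The point holds as a contradiction between the stated method and the stated stratification. Read as written, the BMI tables leave arm sizes and BMI balance exactly as one simple list would. That equality is an identity and needs no assumption. The frequencies for BMI gaps rest on an assumed 30-50% of women above BMI 35, and the completer figures on dropout being random at 30% in every arm.

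The consequence is moderate. The trial remains unbiased and the expected loss of precision is small. What remains is an avoidable tail risk of markedly unequal arms, and of a BMI imbalance that the analysis may leave unadjusted. It should be corrected because the remedy is cheap, not because the trial is unsound without it. The missing category at a BMI of exactly 35 is a wording slip that would affect few women, if any, and carries none of the weight here.

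**What to change.** State the method actually used. If the lists are already blocked or otherwise restricted, replace the word simple in the abstract and in Randomisation and blinding with that method; the cost is a text correction.

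If the lists are unrestricted, generate each BMI table for the remaining allocations from permuted blocks of randomly varying size in multiples of 3 (for example 3 and 6, not blocks of 3 alone). The independent biostatistician should hold the lists, conceal the block sizes from recruiting and exercise staff, and the trial report should describe the change and when it was made. The cost is new lists and a written modification to the ethics committee, as the Ethics section requires. The downside is slightly more predictable allocation in an unblinded trial, limited by the varying block sizes and the concealed list.

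Define the strata so that every eligible woman has one, for example below 35 and 35 or above.

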### Post-intervention assessment

Within 4 days after the final exercise session (HIIT or SSE) or following 12 weeks (Con) the hyperinsulinemic-euglycemic clamp, questionnaires (SF-36, PCOSQ, IPAQ and DASS-21), muscle and fat biopsies, body composition measures (DXA, weight, waist and hip circumferences) and graded exercise tests will be repeated. Women will be asked to abstain from training or physical exercise during this period. An accelerometer will be given (or mailed if in the control group) 7 days before post-intervention testing to assess exercise in this period. They will again be asked to complete a 3-day food dairy.

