### Outcome measurements

Outcome measures will be taken pre-intervention and post-intervention (Fig. 1). The primary outcome is the change in insulin sensitivity (measured by the steady state glucose infusion rate determined during the hyperinsulinemic-euglycemic clamp) between the three interventions. Secondary outcomes include reproductive health via hormone profiles (AMH and steroid profiles), mental health and health-related quality of life, body composition, physical activity behaviours and cardio-respiratory fitness.

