### Hyperinsulinemic-euglycemic clamp

Participants will undergo a hyperinsulinemic-euglycemic clamp to measure insulin sensitivity [3, 46, 47]. Human insulin (NovoNordisk ActRapid) will be infused at a constant rate (40 mU/min/m^2^) while a variable rate glucose solution is infused to meet the target of 5 mmol.L^− 1^ blood glucose in the last 30 min of the clamp. During the clamp, one hand will be warmed to improve blood flow for blood sampling. Blood samples will be taken every 5 min to monitor circulating blood glucose and an additional blood sample will be taken every 30 min during the clamp for insulin analysis. To reduce the risk of low potassium levels (hypokalaemia), participants will be given a single dose (600 mg) of slow-release potassium before the commencement of the insulin clamp.

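### The clamp operator, who adjusts the glucose infusion rate that is the primary outcome, is outside the stated blind and may know the arm at the post-intervention test

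*Protocol article*

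**What the plan says.** All references are to the protocol article.

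- **Randomisation and blinding** gives the reason for open allocation: "As exercise interventions cannot be blinded from participants and staff (accredited exercise physiologists) implementing the intervention". It then sets the extent of the blind: "only staff undertaking sample analysis and endpoint data processing will be blinded to group allocation".
- **Outcome measurements** defines the primary outcome as change in insulin sensitivity, "measured by the steady state glucose infusion rate determined during the hyperinsulinemic-euglycemic clamp".
- **Hyperinsulinemic-euglycemic clamp** says how that rate arises: insulin runs at a constant rate while "a variable rate glucose solution is infused to meet the target of" 5 mmol/L in the last 30 minutes. The feedback is frequent: "Blood samples will be taken every 5 min to monitor circulating blood glucose".
- On timing, **Randomisation and blinding** states "Following baseline testing, participants will be randomised to one of three 12-week interventions", and **Post-intervention assessment** places the second clamp after the intervention: "Within 4 days after the final exercise session (HIIT or SSE) or following 12 weeks (Con) the hyperinsulinemic-euglycemic clamp".

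**The concern.** The primary outcome is not a laboratory value read from a stored sample. It is a rate that someone sets and resets at the bedside in response to glucose readings. Blinded assay work and blinded data processing come afterwards and summarise rates already chosen.

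The justification covers two groups, participants and training staff. Nothing in the document requires clamp staff to belong to either group, so the stated reason does not explain leaving them outside the blind.

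The trial has a declared directional hypothesis in favour of HIIT (Hypothesis). An operator who knows the arm and shares that expectation could, without intending to, adjust the infusion differently between arms. The result would be differential measurement error in the primary endpoint.

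**Working it through.** **1. Who is inside the blind at each step that produces the outcome**

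| Step | Where described | Blinded as written? |
|---|---|---|
| Baseline clamp | Baseline assessment; randomisation comes later | Not exposed: no allocation exists yet |
| Setting the infusion at the post-intervention clamp | Hyperinsulinemic-euglycemic clamp; Post-intervention assessment | No: not among the blinded roles |
| Analysis of samples | Randomisation and blinding | Yes |
| Processing of endpoint data | Randomisation and blinding | Yes |

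Only one of the two clamps is exposed. The outcome is post minus baseline, so a shift of b in the post-intervention rate in one arm appears as a shift of b in that arm's mean change. Nothing at baseline cancels it. The article describes no fixed algorithm or automated control of the infusion and does not say who the operator is.

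**2. Sensitivity of the rate to glucose drift within the window**

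If glucose rises by ΔG over the window, part of the infused glucose has filled the glucose space and has not been taken up. The rate then overstates uptake by

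shift = V × weight × 180.16 × ΔG / (30 min × body surface area)

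Inputs: the 30-minute window (Hyperinsulinemic-euglycemic clamp); 180.16 mg/mmol, the molar mass of glucose; and, as assumptions because the article gives none of them, weight 90 kg, surface area 2.0 m² and V = 0.19 L/kg (range 0.15 to 0.25).

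Per 1 mmol/L of drift:
- V = 0.15: 0.15 × 90 × 180.16 / (30 × 2.0) = 40.5 mg/min/m²
- V = 0.19: 51.3 mg/min/m²
- V = 0.25: 67.6 mg/min/m²

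Drift that would equal the 27 mg/min/m² in the sample size section: 27/40.5 = 0.67, 27/51.3 = 0.53 and 27/67.6 = 0.40 mmol/L. Against the 5 mmol/L target these are 13%, 11% and 8%. The shift is proportional to weight divided by surface area (45 kg/m² here), so a ratio 10% higher or lower moves it by 10%.

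This formula covers change within the window only. If glucose has settled at a steady level above or below 5 mmol/L, ΔG is near zero and the formula returns about zero. It does not measure the effect of a stable offset, and the documents give no figure from which that effect could be calculated.

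**3. What a given bias would do to the test (illustration)**

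For a two-arm contrast with no true effect and a shift b in one arm, P(reject) = Φ(b/SE − 1.96) + Φ(−b/SE − 1.96), with SE = SD × √(2/n) and n = 14 per arm. The article gives no SD of change. The value 108 is 27/0.25, from its stated effect size; the others are assumed.

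| SD of change | b = 10 mg/min/m² | b = 27 mg/min/m² |
|---|---|---|
| 108 | 5.7% | 10% |
| 54 | 7.8% | 26% |
| 34 | 12% | 56% |
| 27 | 16.5% | 75% |

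The nominal level is 5%. A small bias may matter little or a good deal, depending on an SD that is not given.

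**The case against.** **Disclosed limitation, condensed article.** A journal article leaves operating detail to the full protocol. That is a fair answer on steady-state criteria, infusion procedure or a drift correction, and their absence is not held against the plan here. It does not answer the main point, because the article makes a positive statement that only two roles are blinded. A generous reader might count whoever measures glucose during the clamp as sample-analysis staff. That still leaves the setting of the infusion outside the wording. If the sponsor means the blind to reach the bedside, the sentence should say so.

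**The operator knows the arm.** A reader might infer this, but the documents do not say it. They neither name the operator nor say that training staff run clamps. The text supports only that the operator is not blinded and may know.

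**Limited latitude.** This stands. Readings every 5 minutes against a fixed target bound what an operator can do. To reproduce the full 27 mg/min/m², the average net drift would have to differ between arms by about half a mmol/L in the favourable direction, which would fit poorly with a steady state. Drift of that size would also show in readings available to the blinded processor.

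**The outcome is an uncorrected rate.** A reader might infer this too. The article says steady state and cites sources for the clamp method; it neither states nor excludes a correction.

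**The graded exercise test is equally exposed.** Only in part. It serves a secondary outcome. Its stopping rules in Fitness parameters include objective ones alongside the participant's wish to stop, and the participant's own effort stays unblinded whoever runs the test.

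**Conclusion.** The point holds on the text. The stated blind leaves out the person who adjusts the primary outcome at the only clamp that follows allocation, and the reason given does not cover that person. The consequence is a risk of differential measurement bias in the change score. It is not a demonstrated bias, and no size can be predicted from the documents.

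The 0.4 to 0.7 mmol/L figure shows how sensitive the rate is to drift within the window. It rests on an assumed 90 kg, 2.0 m² and distribution volume of 0.15 to 0.25 L/kg. It should not be read as an expected bias, and it says nothing about glucose held steadily off target. The point is worth acting on because the primary endpoint is concerned and the remedy needs no new measurement.

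**What to change.** Amend Randomisation and blinding as follows.

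1. Post-intervention clamps are run by existing team members who do not deliver training and are not told the allocation. The same applies to graded exercise tests where rostering allows. Women are asked not to disclose their arm to assessment staff.
2. The data processor, already blinded, derives the rate over the last 30 minutes and judges whether steady state was reached without knowledge of arm.
3. The processor uses the 5-minute readings to correct the rate for glucose change within that window.
4. The glucose level achieved in the window is reported by arm. This is needed because the drift correction does not remove a stable offset from target; a difference between arms in achieved glucose would reveal one.

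If the trial is already under way, items 2 to 4 can still be applied to every clamp for which the readings were kept.

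Cost: no extra visits or samples, and a few lines in the endpoint derivation. The real constraint is rostering. The article gives no staffing information, and in the exercise arms the second clamp must fall within 4 days of the last session. Some women will disclose their arm, so the operator blind will be imperfect; items 2 to 4 do not depend on it.
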